## Abstract

**Background:**

At the time of surgery, approximately 10–20% of the patients with pancreatic cancer are considered unresectable because of unexpected liver metastasis, peritoneal carcinomatosis or locally advanced disease. This leads to futile surgical treatment with all the associated morbidity, mortality and costs. More than 50% of all liver metastases develop in the first six months postoperatively. These (subcentimeter) liver metastases are most likely already present at the time of diagnosis and have not been identified pre-operatively, due to the poor sensitivity of routine preoperative contrast-enhanced CT (CECT).

**Methods:**

The DIA-PANC study is a prospective, international, multicenter, diagnostic cohort study investigating diffusion-weighted, contrast-enhanced MRI for the detection of liver metastases in patients with all stages of pancreatic cancer. Indeterminate or malignant liver lesions on MRI will be further investigated histopathologically. For patients with suspected liver lesions without histopathological proof, follow up imaging with paired CT and MRI at 3-, 6- and 12-months will serve as an alternative reference standard.

**Discussion:**

The DIA-PANC trial is expected to report high-level evidence of the diagnostic accuracy of MRI for the detection of liver metastases, resulting in significant value for clinical decision making, guideline development and improved stratification for treatment strategies and future trials. Furthermore, DIA-PANC will contribute to our knowledge of liver metastases regarding incidence, imaging characteristics, their number and extent, and their change in time with or without treatment. It will enhance the worldwide implementation of MRI and consequently improve personalized treatment of patients with suspected pancreatic ductal adenocarcinoma.

**Trial registration:**

ClinicalTrials.gov Identifier: NCT03469726. Registered on March 19th 2018 - Retrospectively registered.

## Background

Pancreatic ductal adenocarcinoma (PDAC) is one of the most lethal forms of cancer and expected to become the second leading cause of cancer-related deaths before 2030. Developments in pancreatic cancer diagnostics, surgical techniques and treatment have hardly improved the survival rate in the past 40 years. The 5-year relative survival rate as reported by the American Cancer Society remains only 8% [1, 2].

Only 5–25% of all patients are eligible for surgery, to date the only potential cure [3]. Approximately 40–45% of all patients with pancreatic cancer have metastatic disease at diagnosis and 40% of all patients have locally advanced disease with tumor involvement of surrounding vessels or organs. At the time of surgery, approximately 10–20% of the patients are considered unresectable because of unexpected liver metastasis, peritoneal carcinomatosis or locally advanced disease [4–6].

More than 50% of all liver metastases develop in the first six months postoperatively [7]. These liver metastases are most likely already present at the time of diagnosis and have not been identified pre-operatively, as they are too small to be detected by routine preoperative ultrasound and contrast-enhanced CT (CECT) [8, 9].

CECT is highly accurate in assessing the relationship of the tumor to critical arterial and venous structures, since their involvement can preclude surgical resection. However, CECT has a poor sensitivity (38–76%) for the detection and characterization of liver metastases [7, 10–13], especially for subcentimeter metastases, which are often present in pancreatic cancer [14]. This leads to futile surgical treatment with all the associated morbidity, mortality and costs. Moreover, patients who were explored with curative intent and were found unresectable due to peritoneal or liver metastases had a worse overall survival compared to patients with unexpected locally advanced disease [15].

Nowadays, diffusion-weighted MR imaging (DWI) appears to be valuable in both detection and characterization of focal liver lesions with a high sensitivity (86–97%), even for subcentimeter lesions (60–91%) [16–18]. This technique can be used to detect and characterize liver lesions based on decreased diffusion of water molecules caused by tumoral hypercellularity and reduced extracellular space. DWI is especially useful for detecting subcentimeter liver metastases, it is more accurate than conventional T2-weighted imaging techniques, because signal suppression of intravascular flow is obtained (black blood effect) while maintaining good residual signal of the liver lesions [19]. It is easy to implement and adds very little time to a standard MRI examination. However, without high-quality evidence of the benefit of MRI, the use of MRI as part of the routine workup is questioned and therefore not implemented. Currently most guidelines advise to use MRI as a problem-solving tool in addition to CECT; e.g. when the primary tumor cannot be visualized, or in case of undefined liver lesions [20–22]. The American Society of Clinical Oncology (ASCO) leaves the choice of imaging modality in the hands of the physician [23]. MRI is advised for all patients according to the Japanese guideline; however, the level of evidence is low (grade C) [24].

Most studies that have been performed for liver metastases of PDAC are retrospective, including our single center study in patients with potentially resectable pancreatic cancer without liver metastases on CECT [25]. In this study Gadolinium (Gd) enhanced MRI with DWI detected synchronous liver metastases in 24% of patients with potentially resectable pancreatic cancer on CECT with a sensitivity of 84%. DWI showed more lesions than Gd-enhanced MRI, most of which were particularly small (< 5 mm). Correspondingly, the only prospective study to our knowledge showed that Gd-enhanced MRI, especially DWI, depicted small liver metastases in approximately 10% of patients with a potentially resectable pancreatic cancer without liver metastases on CECT [26]. The reported sensitivity was 73–80% and the specificity 96–100%. However, due to the relatively low prevalence of patients with liver metastases in their study population, in total only 11 patients with liver metastases were included in this study.

In the DIA-PANC study we will determine the diagnostic accuracy of Gd-enhanced MRI with DWI in the detection of liver metastases in patients with all stages of PDAC.

## Methods

### Design

The DIA-PANC study is a prospective, international, multicenter, diagnostic cohort study investigating diffusion-weighted, Gd-enhanced MRI for the detection of liver metastases in patients with pancreatic cancer.

This protocol was written and reported according to the Standard Protocol Items: Recommendations for Interventional Trials (SPIRIT) Guidance and Checklist [27].

### Study population

All patients with (suspected) pancreatic ductal adenocarcinoma are eligible to be included in this study and will be actively recruited at the outpatient clinic by the treating physician. Written informed consent will be obtained by one of the members of the research team. We will include patients until 138 patients with liver metastasis are included, with a maximum total of 465 patients. Exclusion criteria are age below 18 years, previous treatment for pancreatic cancer, concomitant malignancies (except for adequately treated basocellular carcinoma of the skin, subjects with prior malignancies must be disease-free for at least 5 years), contraindications for MRI or CECT (i.e. untreatable contrast allergy, severe renal function impairment, not MRI compatible medical implants), insufficient command of the local language and pregnancy. This study has been approved by the ethical board of our university medical center. Approval of the local medical ethical board is obliged before the start of inclusion in the participating hospitals.

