### Statistics

#### Sample size

The sample size for the study was calculated for the primary endpoint (sensitivity and specificity of MRI for the detection of liver metastases).

The sample size is calculated based on a method for power calculations for diagnostic studies described by Jones et al. [30]. Based on literature and our previously performed retrospective study [9, 31–35] we estimate the sensitivity of MRI will be approximately 90%. In literature the specificity for MRI is usually higher than the sensitivity, therefore we based our sample size calculation on the sensitivity only. With an expected sensitivity of 90%, confidence interval of 95% (Z = 1.96) and α = 0.05, 138 patients with metastasis are required for analysis. Based on literature the expected percentage of patients with liver metastases is approximately 40% [3, 36]. With an expected inclusion rate of 80% (assuming 20% cannot be analyzed optimally, e.g. because no representative liver biopsies could be acquired, mortality before first follow-up or withdrawal) we need approximately 433 patients. In case the proportion of patients with metastases is not equal to 40% in our cohort, we will include until we reach 138 patients with liver metastasis or up to a maximum total of 465 patients.

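### The recruitment stop counts 138 patients with metastasis as included, while the sample size needs 138 for analysis after a 20% loss; read literally, the stop yields about 110

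*Protocol article*

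**What the plan says.** The Sample size section of the protocol article bases the calculation on the sensitivity of MRI alone: "With an expected sensitivity of 90%, confidence interval of 95% (Z = 1.96) and α = 0.05, 138 patients with metastasis are required for analysis". It expects liver metastases in about 40% of patients and then allows for loss: "With an expected inclusion rate of 80% (assuming 20% cannot be analyzed optimally, e.g. because no representative liver biopsies could be acquired"; early death and withdrawal are the other examples. The result is "we need approximately 433 patients".

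The stop rule appears twice:

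- In Study population it carries no condition: "We will include patients until 138 patients with liver metastasis are included, with a maximum total of 465 patients".
- In Sample size it is introduced for the case where the proportion with metastases differs from 40%: "we will include until we reach 138 patients with liver metastasis or up to a maximum total of 465 patients".

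Neither statement says that the 138 must be analysable or confirmed by the reference standard.

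**The concern.** The sample-size text separates patients enrolled from patients who can be analysed and puts a 20% loss between them. The 138 belongs on the analysed side: "138 patients with metastasis are required for analysis". The Study population section uses the same 138 on the enrolled side, so its stop rule drops the allowance that the calculation had just made.

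The Trial status section supports reading *included* as enrolled, since it reports 190 patients included as a recruitment count. If the centres apply the rule that way, recruitment closes with fewer patients for the primary endpoint than the protocol says it requires, although the cap would have allowed more. Recruitment closed too early is hard to recover.

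**Working it through.** **Inputs**, all from the Sample size section: sensitivity 0.90, Z = 1.96, 138 patients with metastasis for analysis, prevalence 0.40, analysable fraction 0.80, stated total about 433, cap 465. The half-width d is not stated.

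**1. Reproduce the plan's figures.** The single-proportion precision formula is n = Z² × p × (1 − p) / d².

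- d = 0.05: 1.96² × 0.9 × 0.1 / 0.05² = 138.3
- d = 0.04 gives 216 and d = 0.06 gives 96

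Of these, only d = 0.05 fits 138, so a half-width of 5 points is a sound inference, but still an inference. The total is 138.3 / 0.40 / 0.80 = 432.2, rounded up to 433. Starting from exactly 138 gives 431.25. The stated figures reproduce.

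**2. What 433 implies.** 138 / 0.80 = 172.5, so about 173 patients with metastasis must be enrolled for 138 to be analysable. 173 / 0.40 = 432.5, which agrees with the plan.

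**3. The stop rule read literally, at 40% prevalence.**

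- Enrolled at the stop: 138 / 0.40 = 345
- Gap to the plan: 433 − 345 = 88 (86 with unrounded figures)
- Analysable with metastasis: 345 × 0.40 × 0.80 = 110.4

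**4. Effect on precision.** Wald half-width = 1.96 × √(p(1 − p)/n).

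| Sensitivity | n = 138 | n = 110.4 |
|---|---|---|
| 90% (planning value) | 5.0 points | 5.6 points |
| 84% (the earlier retrospective study, Background) | 6.1 points | 6.8 points |

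Wilson 95% intervals near 90% are 83.7–93.9% for 124/138 and 83.0–94.3% for 99/110.

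**5. Dependence on the assumptions.**

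- *Prevalence.* The literal rule is reached before the cap when prevalence is at least 138/465 = 29.7%, and it then yields about 110 analysable whatever the prevalence. A rule counting analysable patients reaches 138 within the cap only if prevalence is at least 172.5/465 = 37.1%. At 35%, for example, it runs to 465 and gives 465 × 0.35 × 0.80 = 130.
- *Loss.* At 40% prevalence the unrounded gap is about 38 patients at 10% loss, 86 at 20% and 148 at 30%.

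**The case against.** The strongest reply is that the 138 in the stop rule is the same quantity as the 138 needed for analysis, stated in the same paragraph. Under the Reference standard section, metastasis is established by histology or by growth or increase in number on follow-up imaging. Two of the named causes of loss, no representative biopsy and death before first follow-up, mainly concern patients whose status was never established. Such patients would not count as having metastasis, and taking 20% off again would largely count that loss twice. A cap only 32 above 433 also suits this reading better than an expected stop at 345. All of this is plausible, and if it was the intent there is no shortfall. What remains is that neither statement of the rule says so, and the protocol elsewhere uses *included* for enrolment.

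The condition attached to the rule in the Sample size section also matters. At exactly 40% prevalence that section's own target stays 433, so the conflict at 40% lies between the Study population rule and the 433, not within the Sample size section.

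A reader might go further in three ways that the documents do not support:

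- *That the trial will certainly stop 88 patients early and miss its planned precision.* The 88 depends on the literal reading, 40% prevalence and equal loss, and no planned half-width is stated.
- *That the rule widens the interval from 5.0 to 6.8 points.* This mixes two sensitivities. At 84% the full 138 already gives 6.1, so the rule accounts for 0.7 points.
- *That the running count must rest on imaging suspicion.* The article does not say how the tally is kept, and it may leave that to the full protocol.

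**Conclusion.** The inconsistency is real, and its consequence is conditional. Read literally, with 40% prevalence and the 20% loss falling equally on patients with metastasis, the Study population rule ends recruitment at about 345 instead of 433 and gives about 110 analysable patients with metastasis, 20% fewer than the stated requirement. The loss of precision is modest: about 0.6 points of half-width at 90% sensitivity and 0.7 at 84%. The Sample size section ties no hypothesis test or success threshold to the 138. The point still merits correction before the stop is applied, because a stated size can be missed through wording alone.

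**What to change.** In both Study population and Sample size, state that recruitment continues until 138 analysable patients with liver metastasis confirmed by the reference standard are reached, or 465 patients in total. State the intended half-width as well; 138 implies 5 points.

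If an interim count is needed before follow-up is complete, aim for about 173 included patients with true metastasis, which is about 432–433 enrolled at 40% prevalence. A count of patients suspected on imaging needs an allowance for false positives. As an illustration, take the planned 90% sensitivity and the 88% specificity that the Discussion cites for 3 T MRI. The suspected fraction is then 0.40 × 0.90 + 0.60 × 0.12 = 43.2%, so 173 suspected patients are reached at about 173 / 0.432 = 400 enrolled, which yields only 400 × 0.40 × 0.80 = 128 analysable.

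Note also that 138 analysable fits under the cap only if prevalence is at least about 37%. If the literal rule is kept, restate the expected yield as about 110 analysable and the half-width as about 5.6 points.

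The cost is a rewording in two places. At the planned prevalence and loss it needs no patients beyond the planned 433, and the cap is unchanged.

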### Specific withdrawal of patients

Patients with adenocarcinoma of the distal common bile duct, papilla of Vater or duodenum, patients with a neuro-endocrine tumor or patients with benign tumors will be excluded from analysis and follow-up.

### Primary outcome

The sensitivity and specificity of Gd-enhanced MRI with DWI for the detection of liver metastases in patients with pancreatic cancer.

### Secondary outcomes

The secondary outcomes of this study are: sensitivity and specificity of CECT for the detection of liver metastases; sensitivity and specificity of MRI and CECT for the prediction of resectability; and the effect of the MRI on patient management.

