### Interpretation of MRI and CT

All MRI and CECT scans will initially be evaluated by the local radiologist and the findings will be included in the clinical decision making. The MRI and CECT scans will also be independently evaluated by a second radiologist blinded for findings of the first evaluation and the clinical outcome. If the MRI and CECT of one patient is evaluated by the same radiologist a minimum interval of 6 weeks will be used to minimize the risk of recall bias.

The MRI and CECT scans will be analyzed for local resectability and suspicious liver lesions. Number of liver lesions, lesion size, liver segment, presumed diagnosis of suspicious liver lesions (indeterminate or malignant) and imaging characteristics on MRI will be noted.

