### Reference standard

Indeterminate or malignant liver lesions will be further investigated histopathologically. The first step in obtaining histological proof of suspected liver lesions on CECT and/or MRI is transabdominal ultrasound of the liver. Biopsy will be performed of visible liver lesions and analyzed with routine histological examination. When lesions are not visible or there is no histological proof of the visible lesions, the next step is surgical exploration (laparoscopic or open) in (borderline) resectable pancreatic cancer. In case liver lesions are identified a frozen section is performed. Hereafter, patients are treated according to standard care protocol.

For patients with suspected liver lesions without histopathological proof, follow-up imaging with paired CECT and MRI at 3, 6 and 12 months will serve as an alternative reference standard. Lesions that are growing or increasing in number over time will be considered metastases.

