## Discussion

The purpose of the DIA-PANC trial is to investigate the diagnostic accuracy of contrast-enhanced diffusion-weighted MRI in patients with suspected PDAC for the detection of liver metastases. Additionally, we will evaluate whether performing contrast-enhanced diffusion-weighted MRI will improve the detection of liver metastases compared to CECT by determining the sensitivity and specificity of CECT for the detection of liver metastases.

Despite the good diagnostic performance of MRI for liver metastases, the benefits of MRI remain unclear, mostly because of low level of evidence, heterogeneity, and bias in the performed studies. Two recently published meta-analyses have suggested the results should be confirmed by performing a well-designed and sufficiently powered study directly comparing liver CT and MRI in the same cohort [37, 38].

A major difficulty in the interpretation of the current literature is that most studies are retrospective often only reporting on a subset of patients actually undergoing a resection, patients with borderline resectable tumors, or patients with indeterminate liver lesions on CECT. These patients have a higher probability of having liver metastases. However, in an era of neoadjuvant therapy, local ablative therapy for advanced tumors, expensive targeted therapies, and resection of oligometastases, MRI may be beneficial to patients with all stages of PDAC. Therefore, all patients with suspected PDAC are eligible for inclusion in the DIA-PANC.

MRI field strength, 1.5 T versus 3 T, was a significant factor in the heterogeneity between studies that was found in a meta-analysis. 3 T MRI had a higher sensitivity (89%) and a lower specificity (88%) for diagnosing liver metastasis compared to 1.5 T MRI (sensitivity 80% and specificity 100%) [37]. Because the signal-to-noise ratio and the lesion-to-liver contrast are higher on 3 T MRI than on 1.5 T MRI, it is reasonable that a 3 T MRI permits a higher lesion detection rate [39, 40]. In the DIA-PANC study we plan to perform all MRIs on a 3 T scanner. A potential downside of a multicenter design is the intervendor variability that could occur when comparing the quantitative Apparent Diffusion Coefficient (ADC) value, this variability seems to be more pronounced at 3 T than at 1.5 T [41].

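### Local resectability is verified only in part, and the index tests influence who is verified, so sensitivity for this secondary outcome is not identified and values from explored patients would be biased

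*Protocol article*

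**What the plan says.** Secondary outcomes (Protocol article, Methods) lists "sensitivity and specificity of MRI and CECT for the prediction of resectability". The cohort is not limited to surgical candidates: according to the Discussion, "all patients with suspected PDAC are eligible for inclusion in the DIA-PANC".

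Interpretation of MRI and CT states what is read: "The MRI and CECT scans will be analyzed for local resectability and suspicious liver lesions". It also says of the local radiologist's evaluation that "the findings will be included in the clinical decision making". A second radiologist reads the scans independently, blinded to the first evaluation and to the clinical outcome.

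The section headed Reference standard deals with liver lesions only: "Indeterminate or malignant liver lesions will be further investigated histopathologically". Where ultrasound shows no lesion or there is no histological proof, "the next step is surgical exploration (laparoscopic or open) in (borderline) resectable pancreatic cancer". Where there is still no proof, follow-up imaging decides: "Lesions that are growing or increasing in number over time will be considered metastases". The Analysis section then cross-tabulates MRI and CECT against histopathology and follow-up. It names no surgical or resection outcome as a comparator.

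**The concern.** Sensitivity for resectability needs the number of truly resectable patients among those the scan calls unresectable. Specificity needs the number of truly unresectable patients in that same group. Neither a liver biopsy nor growth of a liver lesion shows whether the primary tumour is locally resectable. The remaining source of truth is surgery, and the scans under evaluation help decide who has it. This is partial verification that depends on the index test.

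At stake is a secondary result that could be published as ordinary accuracy figures although it reflects who was selected for exploration. The selection may also work differently for MRI and CECT, depending on which scan drove the decision, and that would distort the comparison between them. The primary outcome is not affected.

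**Working it through.** **Plan's own figure.** No figure is given for resectability. The sample size for the primary outcome reproduces if the half-width of the confidence interval, which is not stated, is taken as 0.05: n = 1.96² × 0.90 × 0.10 / 0.05² = 138.3. The total is 138 / 0.40 / 0.80 = 431, or 434 with 139, against the stated 433. I use 433 below only as the cohort size.

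**Inputs from Background.** "Approximately 40–45% of all patients with pancreatic cancer have metastatic disease at diagnosis"; a further 40% have locally advanced disease; 10–20% are found unresectable at surgery. Applying these literature shares to this cohort is an assumption.

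**Split of 433 patients.**
- Metastatic: 433 × 0.40 to 0.45 = 173 to 195.
- Locally advanced, taken as not explored: 433 × 0.40 = 173.
- Explored, as the remainder: 433 × (1 − 0.40 − 0.40) = 87, or 433 × (1 − 0.45 − 0.40) = 65. This 15–20% lies inside the 5–25% that Background gives as eligible for surgery (22–108 of 433).

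**Cells, with 'resectable' as the positive call.** First take the limiting case in which every explored patient was called resectable. Let u = 0.10 to 0.20 be the share of explored patients found unresectable, and q the unknown share of unverified locally advanced patients who are truly resectable.
- True positives = explored × (1 − u): 69–78 of 87, or 52–58 of 65.
- False positives = explored × u: 9–17 of 87, or 6–13 of 65.
- False negatives = 173 × q.

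**Sensitivity across all patients** = TP / (TP + 173q). For example, at q = 0.10 with 87 explored and u = 0.10: 77.9 / (77.9 + 17.3) = 0.818. With 65 explored and u = 0.20: 52.0 / (52.0 + 17.3) = 0.750.

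| q | Sensitivity |
|---|---|
| 0 | 100% |
| 5% | 86–90% |
| 10% | 75–82% |
| 20% | 60–69% |
| 100% (bound) | 23–31% |

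**Specificity, local resectability only** (metastatic patients left out) = 173(1 − q) / (173(1 − q) + FP). At q = 0 this runs from 173.2 / (173.2 + 17.3) = 91% to 173.2 / (173.2 + 6.5) = 96%. At q = 1 it is 0%.

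**Specificity, resectability including metastatic status**, with all metastatic patients counted as verified unresectable. The lower bound is at q = 1 with 40% metastatic: 173.2 / (173.2 + 17.3) = 91%. The upper bound is at q = 0 with 45% metastatic: (173.2 + 194.9) / (173.2 + 194.9 + 6.5) = 98%. The sensitivity formula does not change, so sensitivity is no better identified.

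**Explored patients alone.** In the limiting case there are no negative calls, so sensitivity is 100% and specificity 0%. Only the positive predictive value, 1 − u = 80–90%, is informed by data. When some explored patients carry an unresectable call, the table fills, but negative calls remain under-represented. Sensitivity is then too high and specificity too low.

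**The case against.** Several counter-arguments have weight.

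- *Proven metastases are a reference.* Background counts liver metastasis, peritoneal carcinomatosis and locally advanced disease all as causes of unresectability, and the outcome is not worded as local. On that meaning, patients called unresectable do not all lack a reference standard. This stands, and it bounds specificity; not every metastatic patient will have liver disease or confirmation. It does not reach the locally advanced group, on which sensitivity depends.
- *Discordant calls fill the table.* An explored patient may have been called unresectable on the other modality or by the blinded second reader. This stands. A reader might infer that 100% and 0% are fixed by the design, but the document does not support that.
- *Pairing helps.* If every patient called resectable on either scan were explored, ratios of true-positive and false-positive rates between MRI and CECT could be estimated without verifying the double negatives. The MRI–CECT comparison is therefore not necessarily meaningless. The article does not say that this condition holds.
- *The exploration sentence is about liver lesions.* It is a step in the lesion work-up and does not set a rule for who has pancreatic surgery. This stands: that patients judged locally unresectable mostly go unexplored is inferred from it and from the share eligible for surgery in Background.
- *The full protocol may define the outcome.* It may. Treatment data are collected throughout, and Analysis allows further analyses for missing data. These could supply a definition or bounds, but they cannot observe resectability in patients who were never explored.

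**Conclusion.** The point holds for local resectability, which is what the scans are read for. Verification is partial and depends on the index tests. Under the assumed split, about 65–87 of 433 patients would be explored and about 173 would be unverified. Sensitivity across all patients is not identified: its possible range is about 23–100%, and it falls to 75–82% if only 10% of the unverified are truly resectable. Plain sensitivity and specificity from explored patients would be biased by an amount that depends on which scan drove the decision. On the broader meaning of resectability, specificity is bounded at about 91–98% and sensitivity is still open.

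The sizes rest on the literature shares in Background, on locally advanced patients not being explored, and on q, which the documents do not give. The 80–90% predictive value is a historical rate, not attributed to either modality. It also mixes local and metastatic causes of unresectability. It is an illustration, not a forecast. A reader might go further and say that resectability accuracy cannot be studied here at all. The documents do not support that, because predictive values and discordance among explored patients can be reported.

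**What to change.** In Secondary outcomes and Analysis:

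- Make the reported measure the positive predictive value of an MRI call, and of a CECT call, of 'resectable' among explored patients, with 95% CIs and stated as conditional on exploration.
- Tabulate MRI/CECT discordance on resectability against the surgical result.
- Report patients with neoadjuvant therapy between imaging and exploration separately.
- If sensitivity and specificity are kept, state the reference standard for resectability, say whether it is local or includes metastases, and present both measures with verification-bias bounds, not as plain estimates from explored patients.

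This changes neither the sample size nor patient management. The cost is a narrower claim for a secondary outcome and a little more analysis.
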